### Data collection and handling of withdraw and dropout

This is an 18 week clinical trial, in which subjects need to take research medication for 8 weeks, attend 5 assessment visits, obtain 2 sets of blood tests and plain abdominal X-rays, fill in a few sets of questionnaires, complete a patient diary for the entire study period, and stop taking other herbal medication and laxatives. Original data of study forms will be entered and kept on file at the participating site. All the files are to be stored in numerical order and stored in a secure and accessible place. Participant files will be maintained in storage for a period of 5 years.

In order to maximize subjects’ compliance, we first run a thorough consent process for all participants by explaining the details of the study schedule, potential side effects of treatment, and the responsibilities that need to be undertaken by subjects. Second, support and reassurance is provided during the whole study. Third, we will carefully scrutinize subjects (during the 2-week run-in period) to exclude ineligible and potentially low compliance individuals before randomization. Fourth, a direct telephone hotline and email account were established in order to optimize active communication with patients and to respond to enquiries. Furthermore, additional visits can be arranged for patients to see WM doctors or TCM practitioners if patients develop adverse events before the next scheduled visit. If any patient expressed thoughts of withdrawing or dropping out, we would try to help that individual determine the reason, and attempt to resolve any issues, in order to keep the patient in the study.

In order to monitor the reported compliance of the patients, the patients will be required to return the remaining medications at treatment visits except the first visit and last visit. Our research assistant will take a record of each patient. 80% of the consumption will be considered good compliance. If the patients have no bowel movement for at least three consecutive days during the study rescue therapy as dulcolax suppository are provided to the patients.

The trial would be terminated in a specific subject if he/she has: 1) presence of severe adverse effect; 2) hypersensitivity towards research medication; 3) participation in another CHM research project; or 4) presence of life-threatening disease. The whole research plan would be terminated for the following circumstances: 1) presence of serious adverse effect related to the research medication with supportive evidence; or 2) completion of all follow-up assessments.

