**Schedule of enrolment, ****intervention and assessments.**

### Participants

*Setting*: The study was performed at Lee Kee Memorial Dispensary (general outpatient clinic), Li Ka Shing Specialist Clinic of Prince of Wales Hospital and Clinics of the School of Chinese Medicine, and Hong Kong Baptist University. The participants were enrolled from the public through advertisements in local newspaper and out-patient clinics.

*Diagnostic criteria for FC* (*Rome III*) [3]: 1) At least two of the following occurrences more than 25% of the time were required for a diagnosis of functional constipation: straining, lumpy or hard stools, sensation of incomplete evacuation, sensation of anorectal obstruction/blockage, manual maneuvers to facilitate, or fewer than three defecations per week; as well as 2) the rare presence of loose stools without the use of laxatives; and also 3) insufficient criteria for a diagnosis of irritable bowel syndrome.

*Diagnostic criteria for excessive constipation in TCM theory*[6]: Any three of the chief symptom manifestations of Heat and/or Qi stagnation were required for a diagnosis of functional constipation: 1) dry, hard stools; 2) difficult bowel movements; 3) abdominal distension, with or without tenderness; 4) belching; 5) dry mouth or halitosis; 6) red tongue with dry and/or yellow coating; and 7) Wiry pulse.

*Inclusion Criteria*: Patients were included if they had all of the following: 1) met the diagnostic criteria for FC (Rome III); 2) met the diagnostic criteria for excessive constipation in TCM theory; 3) were age 18 to 65 years (inclusive); 4) had a complete spontaneous bowel movement (CSBM) ≦2 times/week (CSBM is defined by feeling of complete passage of stool after defecation, rather than partial or incomplete evacuation, without the use of any laxative or enema within 24 hours) [19]; 5) exhibited severity of constipation ≧3 points (on a 7-point scale) [20]; 6) had a total symptom score ≧8 points (on a 7-point scale for constipation-related symptoms); 7) had a normal colonic examination (barium enema or colonoscopy) within five years; and 8) had a normal liver and renal function in blood test within 3 months.

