### Outcomes

Participants recorded stool frequency, stool form (on the 7-point Bristol stool scale, ranging from 'Separate hard lumps’ to 'Watery’), and feeling of complete evacuation (yes/no). They were also required to log intake of research medication, rescue drug and/or any other medication use throughout the study in a daily diary. Principal investigators (PIs) and research assistants (RAs) interviewed patients at the end of Week 2 (baseline), Week 4 (within treatment), Week 8 (end of treatment), and Week 16 (end of follow-up), for symptoms, compliance, and occurrence of adverse events. Data on global symptom improvement, individual bowel symptoms and stool consistency were collected.

Individual assessment of constipation and related symptoms (severity of constipation, sensation of straining, incomplete evacuation, bloating, abdominal pain/cramping, nausea and passing of gas) were recorded using a 7-point ordinal scale (0 = not at all, 6 = very severe) [see Additional file 2: Table S1] on a designated form that participants filled out during every visit [3]. Global symptom improvement was defined as the participant's subjective feeling of adequate relief of symptoms. For this purpose, participants were asked to rate their impression of changes in constipation by scoring (in comparison with their baseline (Week 2) scores) their impression of these changes from 0 to 6 to represent that they were feeling markedly worse or better at the respective extremes [3]. The response categories are collapsed to simply 'Improved’ for score 4 to 6, 'Same’ for score 3 or 'Worse’ for score 0 to 2 [24].

The primary outcome will be the response rate for CSBM during the treatment period: a clinically meaningful endpoint that combines an objective measure (number of bowel movement) with a subjective measure (feelings of patients as to completeness of defecation) [25,26]. Participants with a mean increase of CSBM ≧1/week compared with the last 14 days of the run-in period are defined as responders.

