Secondary outcomes will include the response rate for CSBM during the follow-up period, including stool frequency, changes from baseline in scores of individual symptom assessment (severity of constipation, sensation of straining, incomplete evacuation, bloating, cramping/abdominal pain, nausea and passing of gas), and global symptom assessment (improved, same or worse). Safety profiles of MZRW will be assessed by determining important adverse events reported in participants’ diaries, in follow-up interviews and in clinical laboratory evaluations (for example, liver and renal function testing). During the last visit, the success of blinding would be evaluated for both investigators and patients, as to whether CHM, WM or placebo had been taken. In particular, patients are asked to rate the appearance, color, texture, taste and efficacy of the medication to try to determine whether these factors were important in their conclusion.

In addition, an objective estimate of changes in colonic transit time is made based on a commercially available radio-opaque Sitzmarks capsule (Konsyl Pharmaceuticals, INC.,Easton, MD 21601,U.S.A).

Each gelatin capsule contains 24 barium sulfate embedded polyvinyl chloride markers measuring 1 mm × 4.5 mm. Plain radiographs of the abdomen are obtained after patients swallow a capsule, for five days (120 hours) before and 8 weeks after the treatment period. Normal colonic transit is defined as expulsion of at least 80% (19 or more) markers [27,28]. For patients with six or more makers scattered throughout the colon, hypomotility or colonic inertia is suggested. If six or more markers are gathered in the rectosigmoid region with a near normal transit of markers through the rest of the colon, functional obstructive or dys-synergic defecation is suspected [4,29].

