### Recruitment procedures

Three strategies are used to recruit participants with FC. The first relies on the participant bank of over 600 patients, built up from prior research team work in functional constipation related studies since 2007. The second relies on referrals from the two study sites (Lee Kee Memorial Dispensary and Li Ka Shing Specialist Clinic of Prince of Wales Hospital) from our co-investigators (Co-Is). The third strategy consists of posted advertisement in local newspapers and a press conference to introduce our research.

All patients diagnosed with functional constipation by the physicians (Co-Is) are referred to the principal investigator (PI) and/or to the research assistants (RA) to determine whether they meet diagnostic criteria of excessive constipation according to TCM theory. There is inconsistency among different TCM practitioners regarding pattern differentiation for FC. If any inconsistency occurs for an individual patient concerning pattern identification, the other senior CMP with more than 20 years clinical practice will be invited to make the diagnosis of TCM pattern independently to ensure the consistence of the diagnosis. The aims, procedures and nature of the study, and possible side effects are explained by the PI and/or the RAs before a written consent form is obtained from each subject who agrees to participate. Moreover, patients are informed that they are free to withdraw at any time during the study. All patients undergo a 2-week, drug-free observation period. Meanwhile, they have to complete a stool and symptom diary to confirm their diagnosis. Blood tests of liver and renal function (blood urea, creatinine, alanine transaminase and aspartate transaminase, alkaline phosphatase and bilirubin), and plain abdominal X-ray for colonic transit study are arranged. Patients are considered eligible for the study if their diaries reflect conformance with the Rome III criteria for a diagnosis of functional constipation, and if they also have normal liver and renal function. Recruited patients will obtain their intervention assignment from the PI and/or RAs.

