### Statistical analysis

All efficacy and safety analyses will be conducted according to the intention-to-treat (ITT) principle. Missing values will be imputed by the last-observation-carried-forward method. The statistical analysis will be performed using the Statistical Packages of Social Sciences (SPSS) for Windows version 16.0. The statistical significance is defined as two-sided *P* value of <0.05. Baseline characteristics will be reported as mean (SD). Baseline differences among the groups will be assessed with the use of Student’s t-test for normally distributed continuous variables and the non-parametric Mann-Whitney U test for non-normally distributed variables. For categorical variables, chi-squared test or Fisher’s exact test will be used. Comparisons between groups will be conducted by using an analysis of covariance (ANCOVA) with baseline as covariate. All items and subscales will be compared between groups for each 6-week treatment using ANCOVA, with treatment group as a factor in the model and baseline as the covariate. The changes from baseline to endpoint of treatment in scores will be tested with repeated measure analysis of variance (ANOVA). Within group differences will be assessed with paired t-test for normally distributed data and Wilcoxon signed-rank test for non-normally distributed data.

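### The stopping rule for individual subjects ends the trial, not just the study drug, after a severe adverse effect, hypersensitivity or life-threatening disease, so planned safety and outcome data are lost in patients selected by tolerability

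*Protocol article*

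**What the plan says.** Three parts of the protocol article bear on this point.

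- **Stopping rule** (Data collection and handling of withdraw and dropout): "The trial would be terminated in a specific subject if he/she has: 1) presence of severe adverse effect; 2) hypersensitivity towards research medication". The list continues with joining another herbal medicine project (trigger 3) and life-threatening disease (trigger 4).
- **Analysis** (Statistical analysis): "All efficacy and safety analyses will be conducted according to the intention-to-treat (ITT) principle", and then "Missing values will be imputed by the last-observation-carried-forward method". No exception is stated for any type of variable or any reason for missingness.
- **Safety data.** The Outcomes section draws the safety profile from adverse events noted in diaries, "in follow-up interviews and in clinical laboratory evaluations". Each subject is to "obtain 2 sets of blood tests and plain abdominal X-rays". The first blood set belongs to the run-in, and under Recruitment procedures patients qualify only "if they also have normal liver and renal function".

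**The concern.** Stopping a drug and leaving a trial are different events. A patient who reacts badly should usually come off the drug, but an intention-to-treat analysis of efficacy and safety needs that patient's later data as much as anyone else's. A rule that ends the trial in the subject makes the protocol itself a cause of missing data, and that missingness depends on how well the treatment is tolerated. The amount could therefore differ between Ma Zi Ren Wan (MZRW), senna and placebo.

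Safety is most at stake. The trial is meant to support conclusions about safety as well as effectiveness, at a dose that the Background section describes as higher than the handbook recommendation. The subjects removed are those whose later course says most about harm. An analysis plan can change how gaps are filled, but it cannot recover data that the protocol stopped collecting.

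**Working it through.** The plan gives no figure on this point, so there is none to reproduce. The check sets the provisions side by side and counts what the schedule would lose.

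**1. What is terminated.** The rule names the trial. The next sentence in the same section uses the same verb for the whole research plan, and one of its end conditions is that every follow-up assessment has been done. In that usage, a terminated trial has no assessments left.

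**2. Whether another provision keeps these subjects in.** There are two candidates, both in the same section. Extra visits for adverse events are optional, come before the next scheduled visit and carry no required test. The retention effort concerns patients who themselves voice thoughts of leaving, not patients removed by rule. Neither provides for scheduled assessment after termination.

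**3. Diary weeks lost.** Study design gives 8 weeks of treatment and 8 of follow-up, so 8 + 8 = 16. For an event t weeks into dosing, the loss is 16 − t:
- t = 0: 16 − 0 = 16 weeks
- t = 8: 16 − 8 = 8 weeks

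**4. Interviews lost.** The post-baseline interviews are at Weeks 4, 8 and 16 (Outcomes). An event before the Week 4 visit loses all 3. One between the Week 4 and Week 8 visits loses 2. This assumes that no assessment made at the time of stopping takes the place of a scheduled one.

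**5. Liver and renal tests.** Two sets planned minus one in the run-in leaves 2 − 1 = 1 after baseline. The text does not date it. If the subject is stopped before it, no scheduled post-baseline laboratory value exists.

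**6. What LOCF does with the gaps.** For a missing second laboratory set, the only scheduled value available is the run-in one, which eligibility requires to be normal. Carrying it forward can hide an abnormal result but cannot create one. Adverse events are different: they are not carried forward, and those after termination are simply not captured.

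**7. Number of patients.** No rate is given for any trigger. As an assumption only, if 1%, 5% or 10% of an arm met a trigger:
- 97 × 0.01 = 0.97, about 1 patient
- 97 × 0.05 = 4.85, about 5 patients
- 97 × 0.10 = 9.7, about 10 patients

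**8. Primary outcome.** The sign of any error depends on what is carried. A subject stopped while responding may be credited with a response that would have faded off drug. A subject stopped before any benefit may be carried as a non-responder who might later have responded. The mix in each arm is unknown, so the documents fix neither size nor direction.

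**The case against.** The strongest reply is that this is a condensed article. It gives one sentence of stopping criteria and does not say that diaries, visits or blood tests cease. An early-termination visit, follow-up of an event to resolution and a repeat blood test are details that a full protocol often holds, and the schedule figure is not shown. Clinical care plainly continues: extra visits to doctors are possible, and code breaks are foreseen for managing the patient. This stands as a limit. The point concerns the rule as worded, and the full protocol may already settle it. It does not remove the point, because the article states a rule rather than staying silent, and the rule ends the wrong thing.

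A reader might also infer more than the documents support:

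- **That LOCF fills in the safety data generally.** It does not. It can apply to scheduled measured values, not to adverse events. The triggering event itself is recorded and is counted under intention-to-treat.
- **That normal laboratory values will be imputed for these patients.** That needs the second set not yet taken, no test at or after the event, and the general LOCF sentence applied to laboratory data. Each is possible; none is certain.
- **That the MZRW and senna comparison is materially distorted.** Any figure in percentage points would need assumed event rates, assumed off-drug response and assumed carried values. Pairing a full on-drug response carried forward with a true response that is wholly off drug would exaggerate the error: an early stopper has little response to carry, and a late stopper's treatment-period mean is mostly on-drug. No such figure should be quoted.

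Trigger 4 might be thought unrelated to harm from the study drug. The text does not say so, and a life-threatening condition could arise on treatment, so it belongs with triggers 1 and 2.

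**Conclusion.** The point holds for the wording as it stands. For triggers 1, 2 and 4 the rule ends the subject's trial, and nothing shown keeps that subject under scheduled assessment. Taken literally, each event during dosing costs 8 to 16 of 16 diary weeks, the later interviews and possibly the only post-baseline liver and renal test, in patients selected by tolerability. This fits poorly with an intention-to-treat analysis of efficacy and safety.

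The overall size is unknown because no event rate is given. The efficacy bias is probably small and its direction cannot be stated. The conclusion rests on a literal reading of the rule and on the full protocol adding nothing. It is a worthwhile improvement to consider, not a flaw that by itself undermines the trial.

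**What to change.** Reword the rule for triggers 1, 2 and 4 along these lines:

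> Study medication is permanently stopped in a subject with a severe adverse effect, hypersensitivity to the study drug or life-threatening disease. Unless consent is withdrawn or the patient's condition prevents it, the subject continues the diary, the scheduled visits and the planned second blood set up to the end-of-follow-up visit (Week 16).

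Trigger 3 can stay as it is. Two additions are needed:

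- **Laxatives.** Keep recording "rescue drug and/or any other medication use throughout the study in a daily diary", and keep the spontaneous-movement condition, "without the use of any laxative or enema within 24 hours", for patients off drug. Say whether the requirement to avoid other laxatives still binds them.
- **Laboratory values.** Report a missing second liver or renal result as missing, not by LOCF.

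**Cost.** This is a minor amendment, going to the two ethics committees that approved the protocol. It uses the diary, visits and blood set already planned, with no new procedures or patients. With 20 subjects enrolled and none finished with treatment at submission, nearly all the benefit was still available then. The downsides are staff effort to retain off-drug patients, some of whom will decline, and bowel data affected by other laxatives. Because laxative-assisted movements do not count, stoppers are pushed towards non-response, and the report should say so.

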## Discussion

This randomized double-blind clinical trial is the third clinical study our team has conducted on the effectiveness of MZRW in FC patients with 'excessive syndrome’ in TCM diagnosis. The first study was the optimal dose determination study comparing three different dose groups [13]. The second trial was to evaluate the effectiveness of the optimal dose determined in the previous study compared to the placebo [13]. To our knowledge, this study is the first study to compare the Chinese herbal proprietary medicine (MZRW) with commonly used laxative in the clinical practice of Western medicine, as well as placebo. This study will complete the investigation of MZRW, for the common condition FC, and seeks to provide supportive data to assist in informing clinical practice. Furthermore, we feel that this sequential approach can be replicated for determining clinical effectiveness of CHM interventions in the future. That is, the sequence comprising first conducting a systematic review [12], then implementing a dose determination study which is followed by a placebo-control trial, and lastly comparing with an active control in blinded clinical trial.

Another key process of the protocol is the use of combined diagnostic criteria for both the western diagnosis of Functional Constipation and the Chinese medicine diagnosis of excessive syndrome. In TCM, 'syndromes’ are the foundation for therapeutic principle. The identification of TCM syndromes in clinical practice is subjective and is highly dependent on personal experience, and thus that is why randomized clinical trials of TCM are often lack of syndrome diagnosis. However, by excluding TCM diagnoses, CHM studies must therefore also lose the most important characteristics of Chinese medicine treatment. In this study, we conduct the trial according to the logistical screening steps both in the specialist clinics of gastroenterology and clinical centre of School of Chinese Medicine in order to retain the optimal Chinese Medicine therapeutic effect. The CM diagnostic criteria were arrived at by consensus of all investigators prior to initiating the trial, and are based on the standard criteria described in *Internal Chinese Medicine* and *Criteria of Diagnosis and Therapeutic Effect of Disease and Syndromes in Traditional Chinese Medicine*.

Our systematic review of Chinese herbal medicine for functional constipation, which compared CHM with placebo/no treatment, conventional western medicine (WM), other CHM, and non-pharmaceutical interventions, also indicated the need to seek strong evidence from well-designed CHM clinical trials. The review analyzed 35 randomized trials of CHM interventions and favored the effectiveness of CHM in comparison with various controls [12]. However, it is difficult to translate the results of such studies due to the low methodological quality, different compositions of the CHM formula and lack of standard dosage preparations or manufacturing processes. Strengths of this trial include our rigorous methodology and strict quality control interventions. We described our method of recruitment, sequence generation, allocation concealment mechanism, and data collection methods in detail. In addition, we reported the CHM intervention, MZRW according to *Recommendations for Reporting Randomized Controlled Trials of Herbal Interventions*[30], including dosage regimen and quantitative description, the indications of CM theory, the standardization of the products, and so on.

The clinical trial protocol serves as the foundation, playing a key role of study planning conduct reporting and appraisal. To facilitate appropriate reference standards for scientific, ethical and safety issues before the trial begins, this protocol has been developed according to Consolidated Standards of Reporting Trials (CONSORT) statement [18], Standard Protocol Items: Recommendations for Interventional Trials (SPIRIT) 2013 [31] and SPIRIT 2013 explanation and elaboration: guidance for protocols of clinical trials [32].

